## Abstract

**Background:**

Existing psychological therapies for bipolar disorders have been found to have mixed results, with a consensus that they provide a significant, but modest, effect on clinical outcomes. Typically, these approaches have focused on promoting strategies to prevent future relapse. An alternative treatment approach, termed ‘Think Effectively About Mood Swings’ (TEAMS) addresses current symptoms, including subclinical hypomania, depression and anxiety, and promotes long-term recovery. Following the publication of a theoretical model, a range of research studies testing the model and a case series have demonstrated positive results. The current study reports the protocol of a feasibility randomized controlled trial to inform a future multi-centre trial.

**Methods/Design:**

A target number of 84 patients with a diagnosis of bipolar I or II disorder, or bipolar disorder not-otherwise-specified are screened, allocated to a baseline assessment and randomized to either 16 sessions of TEAMS therapy plus treatment-as-usual (TAU) or TAU. Patients complete self-report inventories of depression, anxiety, recovery status and bipolar cognitions targeted by TEAMS. Assessments of diagnosis, bipolar symptoms, medication, access to services and quality of life are conducted by assessors blind to treatment condition at 3, 6, 12 and 18 months post-randomization. The main aim is to evaluate recruitment and retention of participants into both arms of the study, as well as adherence to therapy, to determine feasibility and acceptability. It is predicted that TEAMS plus TAU will reduce self-reported depression in comparison to TAU alone at six months post-randomization. The secondary hypotheses are that TEAMS will reduce the severity of hypomanic symptoms and anxiety, reduce bipolar cognitions, improve social functioning and promote recovery compared to TAU alone at post-treatment and follow-up. The study also incorporates semi-structured interviews about the experiences of previous treatment and the experience of TEAMS therapy that will be subject to qualitative analyses to inform future developments of the approach.

**Discussion:**

The design will provide preliminary evidence of efficacy, feasibility, acceptability, uptake, attrition and barriers to treatment to design a definitive trial of this novel intervention compared to treatment as usual.

**Trial registration:**

This trial was registered with Current Controlled Trials (ISRCTN83928726) on registered 25 July 2014.

## Background

Bipolar disorders are characterized by periods of depression and periods of elated or irritable mood (mania or hypomania), with around 2 to 6% of the general population meeting the criteria for diagnosis [1, 2]. The cost of bipolar disorders annually in the UK is £5.2 billion, projected to rise to £8.2 billion by 2026. Despite treatment, people with bipolar disorders remain depressed for the majority of time when not experiencing an episode. After apparent recovery from a bipolar episode, subsyndromal symptoms of depression remain in the long term, estimated at 30 to 50% of subsequent weeks [3, 4]. Depressive symptoms form the largest contribution to impaired functioning in bipolar disorder [5, 6]. At present, antidepressant treatment is relatively ineffective for these individuals [7].

There is a clear need for a more effective, cost-efficient intervention such as CBT (cognitive behavioral therapy). A number of reviews and meta-analyses of existing psychological interventions for bipolar disorders demonstrate mixed outcomes; yet overall, there are significant but modest effects [8–10]. A similar mixed set of outcomes were found in the most recently published trials, with most participants continuing to experience significant sub-clinical symptoms and disruption to life-functioning after receiving an intervention [11–13]. Thus, there remains a need for an alternative approach to managing bipolar disorders. Our group has been developing and piloting a case series for a new CBT approach known as TEAMS (Think Effectively About Mood Swings) based on an empirically supported model [14]. It involves a new integrative treatment approach that has the potential to benefit those people whose symptoms of depression, hypomania and anxiety have otherwise remained treatment-resistant and/or those with reduced functioning.

Our approach specifically targets current problems as specific to the patient, in contrast to earlier forms of CBT for bipolar disorder that have focused on preventing future relapse. In a range of other psychiatric disorders, CBT is also designed to work on current problems. Treatment is focused on developing a formulation (a shared understanding) of how thinking styles and behaviors maintain and escalate current symptoms, such as unipolar depression [15, 16], anxiety disorders [17, 18] and eating disorders [19]. In our own research, people diagnosed with bipolar disorders reported that their recovery involved not simply remaining free of relapse, but also regaining a sense of purpose in their lives and facing their longstanding problems [20, 21].

Therefore, the cognitive model [22] that guides TEAMS focuses on understanding what is maintaining people’s current problems, such as anxiety, depression and irritability, and facilitates people regaining control over their lives. The model proposes that people with bipolar disorders experience mood difficulties because they strive to control their mood in extreme ways, which negatively affects their ability to control and achieve their broader goals in life. As such, their mood rarely reaches a stable state and their attempts to pursue their life goals are disrupted. The goal of TEAMS is to help people to develop awareness of the ways in which they manage their moods and develop alternative ways in which to live a more fulfilling and balanced life.

The current study represents the fourth phase in the development and testing of TEAMS. In the first phase, we conducted a series of literature reviews [23–25] and qualitative analyses of personal accounts [21, 26] to inform our treatment model [22]. In the second phase, we tested the model through a range of self-report, observational and experimental studies that provided strong evidence for the central role of extreme appraisals of internal states as a key mechanism in bipolar disorders and mood swings [20, 27, 28]. In the third phase we reported a number of case studies and a case series [29] that demonstrated promising findings regarding acceptability and effect sizes, and so established the rationale for a pilot randomized controlled trial at the fourth stage. At this fourth stage it is important to establish whether there is evidence that TEAMS added to usual care has evidence of clinical effectiveness of usual care. Hence the TEAMS CBT will be compared to usual care. The fifth stage is envisaged to be a multi-center, definitive randomized controlled trial to establish a more precise estimate of the clinical- and cost-effectiveness of the intervention, as well as the generalizability of the results.

## Method

The study was approved by the London Queens-Square Research Ethics Committee (REC reference: 11/LO/1326).

### Objectives

Our objective is to determine whether the TEAMS approach is feasible and acceptable to individuals with bipolar disorder compared with treatment-as-usual and establish an estimate of treatment effect size to inform a larger definitive randomized controlled trial. We aim to assess the feasibility and acceptability of, and information on uptake, service barriers and attrition needed to design a definitive randomized controlled trials. We predict that TEAMS will reduce symptoms of depression, hypomania and anxiety, improve social functioning and promote recovery in comparison to treatment-as-usual at six months post-baseline (post-treatment in the TEAMS wing), and at 12 and 18-months post-baseline. We also aim to evaluate the clinical- and cost-effectiveness of an intervention which has the potential for direct benefits for patients.

### Trial design

A parallel group rater-blind randomized controlled trial comparing treatment-as-usual with up to 16 sessions of TEAMS therapy. Allocation to the two groups will be at a ratio of 1:1 and have an exploratory framework. The design for this study involves a quantitative component (pilot trial) and a qualitative component (interviews with patients and service providers, described later).

### Primary outcome measure

The main objective of the pilot randomized control trial relates to evaluation of recruitment and retention of participants into both arms of the study, as well as adherence to therapy, to determine feasibility and acceptability. We predict that TEAMS will reduce depression in comparison to treatment-as-usual at 6 and 12 months post-randomization, with the Beck Depression Inventory [30] score at six months as the primary outcome measure.

### Secondary outcome measures

The secondary hypotheses are that TEAMS will reduce the severity of hypomanic symptoms and anxiety, change thinking styles responsible for maintaining symptoms which will be targeted by the therapy, improve social functioning and promote recovery compared to treatment-as-usual at post-treatment and follow-up.

Several secondary outcome measures will be used: a Structured Clinical Interview for Diagnosis Longitudinal Interval Follow-up Evaluation (SCID-LIFE) interview for episodes of mania or depression [31], interview measures of manic symptoms (Bech-Rafaelson, [32]) and depression [33], composite internal state scale score (ISS, [34]), anxiety as measured by the Generalised Anxiety Disorder 7 item scale GAD-7 [35], recovery as measured by the Process of Recovery Questionnaire (QPR) [36], cognitive style measured by the Hypomanic Attitudes and Positive Predictions Inventory [37, 38], the EuroQol Health Status Measure (EQ-5D) [39] and session-by-session measures. Raters were trained at the beginning of, and during the study, in interview measures of outcome by an experienced rater who is a consultant psychiatrist (RM), to improve the reliability and validity of the ratings. Participants are paid a fixed amount of expenses for their time (£10 per assessment after baseline) and travel for the follow-up assessment sessions. If any participant withdraws from treatment, we will seek permission to collect outcome data. If a participant misses their assessment, they are contacted a maximum of three times by the rater through the means of contact that they have specified (such as a home or mobile telephone, letter or care coordinator), after which they are coded as missed and re-contacted for the next follow-up point. Self-report measures are collected where interview assessments are not possible.

Prior to each session, the clients complete the ISS and a personalized 10 to 15 item Client version of the Hypomanic Attitudes and Positive Predictions Inventory. (HAPPI) (Client-HAPPI) which assesses their most prominent beliefs about internal states [29]. At the end of each treatment session, clients rate their level of satisfaction with therapy on a Likert scale from 0 (not at all) to 10 (extremely). Adherence is evaluated by the widely used revised version of the Cognitive Therapy Rating Scale (CTS-R) [40], and a brief checklist of adherence specific to the TEAMS model - The TEAMS Treatment Adherence Checklist (T-TAC).

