### Control condition group

The control condition consists of treatment-as-usual which typically involves regular meetings with a care coordinator, access to a psychiatrist, medication and monitoring of risks that require immediate intervention. Treatments, including other psychological interventions, are not withheld in the treatment-as-usual group but are monitored using a treatment documentation sheet. Following written consent, participants are randomized within two working days.

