### Randomization and blinding

–The independent Manchester Academic Health Science Centre Clinical Trials Unit conducts anonymized randomization in a permuted blocks design with block sizes varying randomly between 8 and 12. There is no stratification of the sample, but baseline information may be used in a *post hoc* manner to explore the effects of baseline characteristics. The procedure is as follows. An administrator contacts the clinical trials unit with a password and the participant identification number, and receives an allocation sequence to assign participants to either group. The administrator then directly contacts participants and therapists. Due to the nature of the trial only a single blinding (of raters) is needed. Blindness of raters is ensured using a variety of procedures, including separate offices for therapists and research assistants, briefings to participants prior to assessment and encryption of randomization information. Unblindings are regularly monitored and recorded. Deliberate unblinding would only occur if there was a serious adverse incident such as suicide or violence to another person by a participant.

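### Having the blinded rater trace people who miss assessments, possibly through the care coordinator, creates an avoidable risk of unblinding for the secondary interview outcomes

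*Protocol article*

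**What the plan says.** Under Secondary outcome measures, the protocol article fixes who follows up a missed assessment and how: "they are contacted a maximum of three times by the rater through the means of contact that they have specified". The examples of routes are "such as a home or mobile telephone, letter or care coordinator". After that the visit is coded as missed and the participant is approached again at the next time point.

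Under Control condition group, usual care is described as typically involving "regular meetings with a care coordinator".

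Under Randomization and blinding, the article states: "Due to the nature of the trial only a single blinding (of raters) is needed". An administrator "receives an allocation sequence to assign participants to either group", and the text continues: "The administrator then directly contacts participants and therapists". The protective measures given as examples are separate offices for therapists and research assistants, "briefings to participants prior to assessment", and encryption of the randomization information. The same section adds that unblindings are regularly monitored and recorded.

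**The concern.** Blinding in this trial rests on one role, the rater. The article gives that role a task that can involve unscripted talk about a patient's current care. A call to a care coordinator about someone who did not attend can easily touch on what treatment that person is receiving or has stopped. TEAMS is given on top of usual care, so a coordinator may be seeing patients from either arm.

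At stake are the outcomes that depend on the rater's judgement: the Hamilton depression rating, the Bech-Rafaelsen mania scale and the SCID-LIFE relapse ratings. Exposure would not be spread evenly over the sample. It would arise only in people who miss visits, and their later ratings bear on relapse and dropout. The trial is also meant to supply effect sizes and procedures for a definitive trial, so a weak tracing procedure could be carried forward.

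**Working it through.** No figure in the article bears on this point, so the check is to set the relevant sections side by side.

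1. **Who does the tracing.** Secondary outcome measures names the rater. This is a stated assignment, not a detail left open.

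2. **Who must stay blind.** Randomization and blinding names raters and nobody else. The tracing task therefore sits with the one role that has something to lose from it.

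3. **Who is told the allocation.** The administrator receives it and then contacts participants and therapists. The text after Figure 1 says that participants are informed by letter. Care coordinators are not named as being told. Nothing stated prevents them from learning it from the patient or mentioning it to a rater.

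4. **Which routes lead to a third party.** Telephone and letter reach the participant. Only the care-coordinator route brings in someone else, and it applies only where the participant specified it.

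5. **What the listed safeguards cover.**
   - Separate offices deal with contact between therapists and raters.
   - Briefings deal with what participants say, and are tied to the assessment. The article does not say whether they also precede a tracing call.
   - Encryption deals with stored information.
   - Recording unblindings detects a breach but does not prevent it. The article states no re-rating by a second rater.
   - None of these explicitly addresses a conversation between a rater and a care coordinator.

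6. **Which outcomes could be affected.** In Table 1 the BDI carries the self-report mark. HDRS, the mania scale and SCID-LIFE do not, and the footnote says that unmarked measures are administered by a researcher as a clinical interview. Under Primary outcome measure, the BDI at six months is the primary clinical outcome, and recruitment, retention and adherence form the main objective. Interviewer bias would therefore reach secondary outcomes only.

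7. **In whom.** Four things must all happen: a participant misses a visit, the contact discloses the allocation, the participant returns, and the same rater then conducts an interview. The article gives no rate for any of these, and it allows self-report measures to be collected where an interview is not possible. The number affected cannot be derived.

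**The case against.** The strongest reply is that who telephones non-attenders is an operational matter and the article contains no contradiction. The list of safeguards is introduced as examples, and the full protocol may hold instructions for raters' contacts. Unblindings are monitored. Raters already interview participants at four follow-ups, and Table 1 includes a researcher-administered service-use interview each time. That offers more opportunity for disclosure than up to three rebooking contacts. All of this stands and limits the weight of the point. It does not remove it, because the article itself gives the task to the blinded role.

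A second reply concerns the remedy. Retention in both arms is a main feasibility outcome, and chasing by blinded raters keeps the effort independent of arm. Giving the task to an administrator who knows the allocation could make persistence differ between arms. This also stands, and it shapes the fix.

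Two stronger readings are tempting and should be resisted:

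- A reader might infer that raters are in fact unblinded by these calls. The article does not support this. It does not say that coordinators know the allocation. Even a remark about stopped therapy would not be conclusive, since other psychological treatments are not withheld in the control arm.
- A reader might put a count on the problem by applying the 29% attrition allowance under Sample size to the 84 participants (0.29 × 84 = 24.4, about 24 people). That allowance is for people lost by 12 months, not for missed visits. Someone lost for good is not interviewed again and cannot be rated by an unblinded rater. Any share assumed to disclose the allocation would also be invented.

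**Conclusion.** The point holds as an avoidable risk to the only blinded role. The listed safeguards do not explicitly cover it, beyond recording breaches once they have occurred. Its reach is narrow: secondary interview outcomes, in participants who miss a visit and are later interviewed by a rater who learned the allocation while tracing them. Interviewer bias does not reach the scoring of the six-month BDI, and the main feasibility objective does not depend on interviewer judgement. The size cannot be computed from the article, so no number is offered.

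The conclusion assumes that a care coordinator may know, and may mention, whether a patient is receiving TEAMS. That is plausible but not stated. This is a cheap improvement, not a flaw that threatens the trial's main conclusions.

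**What to change.** Amend the tracing sentence under Secondary outcome measures so that an existing team member who does not rate outcomes makes the contacts, up to the present limit of three and by the present routes. If not all contacts can be moved, move at least those that go through the care coordinator. Someone who does not know the allocation is preferable; the administrator described under Randomization and blinding is a workable alternative. The script and contact limit should be identical in both arms, the script should ask the person contacted not to mention treatment to the rater, and the rater should receive only the rebooked date or a missed code.

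The cost is a change of wording and some staff time. If the person chosen knows the allocation, there is also a small risk that chasing differs by arm and so affects retention. The fixed script and the three-contact cap limit that risk. Trial status says that participants were still being recruited, so later follow-ups could benefit.

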### Think Effectively About Mood Swings therapy

The TEAMS approach involves an individualized treatment plan of CBT based on the integrative cognitive model of bipolar disorder [22]. Specific treatment strategies and therapy techniques employed are determined by an individual formulation using the model. There are several published descriptions of the intervention, as well as a therapy manual in development [14, 22, 29, 41].

### Control condition group

The control condition consists of treatment-as-usual which typically involves regular meetings with a care coordinator, access to a psychiatrist, medication and monitoring of risks that require immediate intervention. Treatments, including other psychological interventions, are not withheld in the treatment-as-usual group but are monitored using a treatment documentation sheet. Following written consent, participants are randomized within two working days.

### Randomization and blinding

–The independent Manchester Academic Health Science Centre Clinical Trials Unit conducts anonymized randomization in a permuted blocks design with block sizes varying randomly between 8 and 12. There is no stratification of the sample, but baseline information may be used in a *post hoc* manner to explore the effects of baseline characteristics. The procedure is as follows. An administrator contacts the clinical trials unit with a password and the participant identification number, and receives an allocation sequence to assign participants to either group. The administrator then directly contacts participants and therapists. Due to the nature of the trial only a single blinding (of raters) is needed. Blindness of raters is ensured using a variety of procedures, including separate offices for therapists and research assistants, briefings to participants prior to assessment and encryption of randomization information. Unblindings are regularly monitored and recorded. Deliberate unblinding would only occur if there was a serious adverse incident such as suicide or violence to another person by a participant.

### Sample size

The primary aim of this study is to evaluate feasibility, therefore a formal power calculation is not appropriate. However, estimates indicate that with 42 participants per group, using a t-test with a two-tailed significance level of 0.05, we will have over 80% power to detect an effect size of 0.8. If the significance level were altered to 15%, 30 participants per group will have 80% power to detect an effect size of 0.6. A previous case series of seven patients generated a pre-post effect size at one-month follow-up on the primary outcome measure of 3.0, and between 0.7 and 1.4 for the secondary measures [29]. The above information makes a feasibility trial of 30 participants per group an appropriate target.

In aiming for 60 participants in total, the target recruitment is 84 participants, allowing a 29% attrition rate by the 12-month post-randomization point. This dropout rate was based on a conservative estimation just above the highest reported rate of attrition found in other published studies of CBT for bipolar disorder (13 [42], 25 [43] and 21% [10]).

